For CSF biomarkers, the following fluid levels are considered: threonine-181 (p-tau), total-tau (t-tau), amyloid-beta Aβ1-42, Aβ_1-42/1–40_ ratio, Aβ_1-42_/p-tau ratio. ^18^Fluorodeoxyglucose positron emission tomography (^18^F)FDG-PET is analysed with voxel-based single subject using the optimised procedure based on statistical parametrical mapping (SPM), involving a large database of normal controls for comparison and the new FDG atlas for normalisation [10, 11]. Two techniques are used to compute the right and left hippocampal volumes, normalised to the intracranial volume in volumetric MRI. The first technique is ACM-Adaboost, which is a machine learning algorithm used to classify the voxels belonging to the hippocampal region. The second technique is Freesurfer v6.0, which is a surface-based approach [12]. Seven parameters of Small World (SW) are computed in delta, theta, alpha1, alpha2, beta1, beta2 and gamma frequency bands to evaluate the brain connectivity via graph theory in EEG [13]. As part of the study, each participant is required to undergo all necessary tests for biomarker acquisition. These tests are required to be completed within 60 days from the neuropsychological battery assessment and the acquisition of informed consent at the beginning of the study. Biomarker testing is conducted in a blinded manner, meaning that the data collected at baseline, including predictor variables such as biomarkers and any information related to medical history or clinical examination, are not taken into account during biomarker testing. Moreover, to improve the predictive accuracy of biomarkers, clinical and demographic characteristics will be also considered. A critical review of the relevant literature was conducted to identify factors associated with the development of dementia [14, 15]. The following predictors, selected according to the clinical relevance among all the demographic and clinical variables collected, will be used in the development and validation of the multivariable prediction model: sex, age, level of education (measured in years of education), type of MCI (amnesic, non-amnesic) according to single or multiple domains, Amsterdam IADL (short version) [16], Cumulative Illness Rating Scale (CIRS) including severity and comorbidity index [17], hypertension, family history of dementia, smoking status, status of cohabitation as a proxy of social isolation, psychiatric disease (past and present) and cardiovascular disease. All these data, collected during the clinical assessment visit, could significantly improve the accuracy of the prediction model. All predictors are collected at baseline.

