#### Statistical model and variable selection

Initially, an analysis of socio-demographic and clinical variables will be conducted using the Cox model to identify a core of variables significantly associated with the outcome that will be included in the development of the prognostic multivariable model. A check of multicollinearity between predictors will be assessed, then a stepwise selection starting from the full model will be applied using a threshold of 0.10 for removal and 0.05 for re-admission of variables. A final check of variables not selected by stepwise will be conducted using the likelihood ratio test [36, 37]. Age and sex will be forced in the procedure selection and retained in the final model. Subsequently, these selected variables will be included in multivariable models with the addition of individual biomarkers one at a time. The additional predictive value of each biomarker beyond clinical and socio-demographic variables will be calculated. The performance results will be used to determine for each biomarker which form (continuous or categorical) will be chosen for the development of the multivariable prediction model. Categorisation is typically preferred for the application in clinical practice, but as any categorisation implies a loss of information, we will select the biomarker in a categorical form if the loss in performance could be considered negligible with respect to the continuous form. Categorisation will also be chosen in cases where non-linearity is detected for the continuous form. The categorisation according to the threshold provided by the experts (Table 3) will be preferred in case a small loss of performance is observed compared to the continuous form.

The final predictive model will be identified through a multivariable model considering as eligible predictors all the biomarkers and all selected predictors among the clinical and socio-demographic variables using the stepwise selection procedure as described above. Age and sex will be forced into the model selection process. A final check of the result from the automatic selection procedure will be conducted to ensure that no significant biomarkers were excluded and, vice versa, that no negligible biomarkers were included.

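### Clinical predictors other than age and sex are selected without the biomarkers and not re-checked once the biomarkers are in, so one that is masked at the first stage can be left out of the final model

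*SAP article*

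**What the plan says.** The Predictors section says that the listed demographic and clinical variables "will be used in the development and validation of the multivariable prediction model: sex, age, level of education", followed by type of MCI, Amsterdam IADL, CIRS, hypertension, family history, smoking, cohabitation, psychiatric disease and cardiovascular disease.

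The section on statistical model and variable selection then sets the order of work:

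1. It opens with "Initially, an analysis of socio-demographic and clinical variables will be conducted using the Cox model to identify a core of variables significantly associated with the" (the sentence goes on to name the study outcome). No biomarker is in this model.
2. Within that set, "a stepwise selection starting from the full model will be applied using a threshold of 0.10 for removal and 0.05 for re-admission of variables".
3. "A final check of variables not selected by stepwise will be conducted using the likelihood ratio test". This sentence comes before any biomarker is mentioned as entering.
4. "Age and sex will be forced in the procedure selection and retained in the final model". No other variable has this protection.
5. "Subsequently, these selected variables will be included in multivariable models with the addition of individual biomarkers one at a time".
6. The final stepwise model is run "considering as eligible predictors all the biomarkers and all selected predictors among the clinical and socio-demographic variables".
7. The result of that last step is checked "to ensure that no significant biomarkers were excluded and, vice versa, that no negligible biomarkers were included".

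The sensitivity analyses repeat the selection with other p-value thresholds, with the Akaike criterion and with LASSO. They do not say whether clinical variables dropped at the first stage return as candidates. Internal validation repeats the stepwise procedure in 500 bootstrap samples.

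**The concern.** The final model is meant to give an individual 3-year risk from clinical variables and biomarkers together, and the nomogram and risk groups are built on it. The contribution that matters for a clinical variable is therefore the one it makes with the biomarkers in the model. The plan judges ten of the twelve listed clinical items, all except age and sex, only in a model without them.

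The two models can disagree. If a variable is associated with more pathology but, at a given level of pathology, with slower conversion (or the reverse), the two effects offset each other. The variable then looks null when tested without the biomarkers and informative when tested with them. The plan drops it at the point where it is masked and has no later step that looks at it again. Biomarkers do get a check against wrong exclusion at the end; clinical variables do not.

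Education shows how this could arise, though the document does not show that it does. MMSE and delayed recall count among the biomarkers and are described as adjusted for age and sex, or for age only. If schooling raises the score, then at equal scores the more educated patient may be further advanced, while education alone looks neutral.

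**Working it through.** **Selection sequence.** Steps 1 to 3 contain every test that a clinical variable other than age and sex faces before the candidate set is closed, and none includes a biomarker. Step 6 admits only the survivors, and step 7 names biomarkers only. On the plain wording, a variable dropped in steps 1 to 3 is never tested with a biomarker in the model.

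**The plan's own figures.** No stated figure bears directly on the point. The nearest is the candidate budget in the Sample size section, which reproduces. With R² = 0.31 and a target shrinkage of 0.9 (assumed; the article does not state it), the number of patients per parameter is 1 / [(0.9 − 1) × ln(1 − 0.31/0.9)] = 23.68. Events per parameter are 23.68 × 0.16 × 2.5 = 9.47 (stated 9.5), and 400 / 23.68 = 16.9 (stated 17).

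**Mechanism.** For a standardised clinical variable with conditional log HR b_c, and a standardised biomarker with log HR b_m and correlation ρ with it, the log HR seen without the biomarker is approximately b_c + ρ × b_m. When b_c is close to −ρ × b_m, little is left to detect.

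**How often this loses the variable.** A Cox simulation used 400 patients (the evaluable number in the Sample size section), 40% events (16% × 2.5 years), one clinical variable and one biomarker, with 1000 runs per row. All effects and correlations are assumptions. Lost means p ≥ 0.10 without the biomarker and p < 0.05 with it.

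| ρ | b_c | b_m | b_c + ρ·b_m | p < 0.10 without biomarker | p < 0.10 with biomarker | Lost |
|---|---|---|---|---|---|---|
| 0.3 | −0.21 | 0.70 | 0.00 | 9% | 84% | 69% |
| 0.4 | −0.30 | 0.75 | 0.00 | 10% | 96% | 86% |
| 0.3 | −0.30 | 0.90 | −0.03 | 12% | 97% | 83% |
| 0.2 | −0.20 | 0.70 | −0.06 | 17% | 78% | 51% |
| 0.4 | −0.20 | 0.70 | +0.08 | 25% | 73% | 59% |
| 0.2 | −0.30 | 0.70 | −0.16 | 55% | 98% | 40% |
| 0 | +0.30 | 0.70 | +0.30 | 95% | 98% | 2% |
| 0.3 | +0.20 | 0.70 | +0.41 | 100% | 75% | 0% |

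Further from cancellation the loss falls. In 300-run checks with b_m = 0.70 it was 27% for b_c = −0.40 at ρ = 0.3 (sum −0.19), and 12% for b_c = −0.30 at ρ = 0.1 (sum −0.23).

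**What the loss costs in prediction.** With one clinical variable and one biomarker, under masking (biomarker HR 2.0 to 2.2 per SD, ρ 0.3 to 0.4, conditional clinical HR 0.67 to 0.81 per SD), leaving the variable out lowered the out-of-sample c-index by 0.006 to 0.021. A setting closer to the plan, with ten clinical variables, four biomarkers, 400 patients and about 43% events, gave a gain of about 0.004 to 0.007 from re-testing the dropped variables at the end. Without masking, the same re-test changed the c-index by −0.0002 to +0.0003.

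**What the re-test costs.** If all ten non-forced items were dropped and uninformative, about 10 × 0.05 = 0.5 would re-enter by chance. In the ten-variable simulation it was about 0.1 per run.

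**The case against.** The clinical-first order has a purpose. The stated aim is to identify a biomarker or set of biomarkers, and the plan measures each one's added value by NRI, difference in c-statistic and likelihood ratio test. That needs a clinical core fixed beforehand. This stands, and it is a reason to leave the first stage alone. It is no reason to close the candidate set for the final model.

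A reader might infer that the Predictors section and the selection section contradict each other, since the listed variables are said to be used in development yet may never reach the final step. They do not conflict: a variable entered in the first-stage full model has been used in development.

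The final step refers back to the stepwise procedure already described, which could be read as carrying the likelihood ratio check of non-selected variables with it. The reading is possible but weak, because the eligible clinical variables have by then been limited to the survivors and the closing check mentions biomarkers only. LASSO on the full list would show a lost predictor, but its candidate set is not stated and a sensitivity analysis does not define the final model.

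The simulations are also favourable to the concern. The highest loss rates come from effects chosen close to cancellation. The one-variable version leaves out the other clinical variables in the first-stage model, such as MCI type, IADL and CIRS, which may track pathology and partly unmask the variable. Both criticisms stand. The ten-variable simulation allows for several clinical variables, and its gain is correspondingly smaller.

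**Conclusion.** The point holds as a conditional weakness and a cheap improvement. As written, the plan gives a clinical predictor other than age and sex no stated test in the presence of biomarkers once it has been dropped. If such a variable is correlated with a biomarker and its direct effect runs the opposite way, it can be omitted although it would help. Under assumed masking the loss is roughly 0.004 to 0.02 in c-index. Without masking there is none.

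Two stronger readings are tempting and unsupported. The first is that a useful predictor will probably be lost. The loss rates in the table describe the chosen scenarios; no figure in the document gives the sign, size or correlation of any clinical effect, so they are not probabilities for this trial. The second is that the nomogram would give wrong risks. A model that omits a covariate can still be calibrated given the predictors it contains; its predictions are less individualised.

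**What to change.** Keep the first stage as it is for the added-value analyses. Extend the closing check in the section on statistical model and variable selection along these lines: after the biomarkers have been selected, each clinical or socio-demographic predictor dropped at the first stage is tested once by likelihood ratio test against the final model and re-admitted if p < 0.05, the plan's own re-admission level. State under Internal validation that this step is repeated in each of the 500 bootstrap samples. It would also help to state the candidate set for the LASSO and alternative-threshold analyses.

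The cost is a few lines of text and up to ten further tests. No new data are needed, and the candidate count to set against the stated limit of 17 does not grow, because these variables were already candidates. The downside is somewhat more data-driven selection, with an occasional uninformative variable re-entering (well under one on average). The bootstrap correction covers this provided that the re-test is inside the loop.

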#### Checking assumptions and variable handling

The relationship between study outcome and each continuous predictor will be explored. Linearity will be tested. Transformation or categorisation of variables will be considered for dealing with non-linearity. Collinearity between predictors will be measured with the variance inflation factors (VIF) [38, 39]. Values equal to 1 indicate that variables are not correlated, VIF values greater than 5 are generally considered a cause of concern, and values exceeding 10 are indicative of problematic multicollinearity that needs to be corrected. The proportional hazards assumption will be tested using Schoenfeld residuals and checked by visual inspection of the log–log plot. If the assumption is not satisfied, the variable by time interaction will be included in the model.

#### Predictive performance

For each biomarker in the categorical form, the accuracy measures (sensitivity, specificity, positive predictive value, negative predictive value, overall accuracy, positive and negative likelihood ratios) will be calculated for comparison with the literature. For continuous biomarkers, the area under the receiver operating characteristic curve (AUC) will be also reported. Moreover, a univariate analysis will be conducted using the proportional hazard Cox model.

To evaluate the performance of the prediction models, several measures will be considered. The concordance c-index with its 95% CI will be provided as a discrimination measure and the extensions of binary AUC to survival analysis proposed by Harrell will be used [40, 41]. The Akaike information criterion will be provided as a measure of the goodness of fit of the model.

The added value on performance of each biomarker to the multivariable model with demographical and clinical variables will be assessed by the category-free Net Reclassification Improvement (NRI), which is the net proportion of events reclassified correctly plus the net proportion of non-events reclassified correctly. The delta AUC (difference in c-statistics) will be also provided [41], and the likelihood ratio test will be used to assess the statistical significance of the incremental contribution of each biomarker [36, 37].

In addition, to assess the predictive performance of the final multivariable model, calibration measures will also be reported [38, 42]. A calibration plot will be done by plotting the observed outcome proportion (on the *y*-axis) versus the ordered predicted outcome probabilities (on the *y*-axis) by quantile of the predicted risk. Subsequently, the calibration intercept and slope and their 95% CI will be estimated. There is a perfect calibration when the intercept is zero and the slope is one. Moreover, overall measures of performance, the Nagelkerke’s *R*^2^ and the Brier score, will be provided. The Brier score is a composite measure of discrimination and calibration with lower scores indicating improved model accuracy, and it will be calculated at a fixed time point (3 years).

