
### Sample size

To determine the sample size, the methodological work of Bujang and Adnan [18] was followed. This work provides guidance for estimating the minimum sample size required in a screening or diagnostic study to achieve the desired sensitivity and specificity with adequate power and a controlled level of type I error. Based on the literature review, the level of sensitivity for the biomarkers under study ranges between 52 and 81%, while the specificity ranges between 52 and 86%. After a follow-up of about 2.5 years, the incidence of AD in a cohort of individuals with MCI was observed to range from 29 to 46% [19, 20]. Based on this data and utilising the tables provided by Bujang and Adnan, a minimum sample size of 388 individuals with MCI is needed assuming an expected incidence of AD of 40% after a 3-year follow-up period, a sensitivity value of 80% for an individual biomarker (working hypothesis), a power ≥ 80% and a *p*-value lower than 5%. Additionally, applying the formula described by Buderer [21] which incorporates the event frequency into the sample size calculation, it was verified that 400 evaluated individuals would ensure an acceptable level of precision (the half-width of the 95% CI) between 4 and 7.5% for both sensitivity and specificity (Table 2). Assuming a dropout rate of 20%, a total sample of 500 individuals with MCI has been determined.

**Table 2 Tab2:** Level of precision^a^ on the estimates of sensitivity and specificity (for a range of values) corresponding to a sample size of 400, according to an incidence of AD ranging from 27 to 40%

Incidence	Sensitivity			Specificity		
	**80%**	**85%**	**90%**	**80%**	**85%**	**90%**

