**CSF biomarkers**		
Aβ (1–42)	≤ 640 pg/ml	Bellomo et al. 2021 [28]
Total-tau	≥ 404 pg/ml	Bellomo et al. 2020 [29]
Phosphorylated Tau 181 (p-Tau)	≥ 56 pg/ml	Bellomo et al. 2020 [29]
Ratio Aβ_1-42/1–40_	≤ 0.068	Doecke et al. 2018 [30], Leitão et al. 2019 [31]
**Ratio** Aβ_1-42 /p-Tau_	≤ 11.8	Leitão et al. 2019 [31]
**EEG**	Classified in physiological vs pathological based on Small World for the seven EEG frequency bands using machine learning technique	Vecchio et al. 2023 [32]
**FDG-PET**	Classified in negative and positive (AD-like, other forms) using the optimised SPM procedure	Della Rosa et al. 2014 [10], Perani et al. 2014 [11]
**APOE- e4**	Classified in none, one allele, both the alleles	

However, these cut-offs were determined to discriminate between normal cognition and AD, but the population under study is at higher risk of developing dementia compared to the normal population. Therefore, for continuous biomarkers the receiver operating characteristic (ROC) curves will be used to identify new optimal cut-offs for the specific population under study. For biomarkers known to be influenced by sex and/or age, the corrected values will be used. In this context, sensitivity and specificity are both considered targets for determining the optimal cut-off; therefore, among all the commonly used methods [33], the distance to the left-upper corner was chosen. This method maximises both sensitivity and specificity and guarantees a better balance between the two measures [34]. Warnings are raised about its use as not always the method leads to an optimal cut-off in the intention of maximising overall correct classification rates compared to the commonly used Youden’s method [35]; therefore, Youden’s method will be also provided for comparison.

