### Model presentation and risk groups

For each predictive model, the hazard ratios with 95%CI and *p*-value will be reported. For the final predictive model, a nomogram will be generated. A nomogram is a graphical representation of the statistical predictive model. It is a visual tool that translates model numeric results into a visual format, making it easier to estimate an outcome based on multiple variables. Each variable occurrence is assigned a specific score based on its contribution to the overall prediction. The total score from all variables is then used to estimate the probability of the predicted event (in this case, the conversion to AD at 3 years) conditioning to the individual characteristics [45]. For this purpose, the covariates in the Cox model will be centred. Sensitivity and specificity corresponding to different thresholds of the prediction risk score will also be provided for the final model. Finally, three or more risk categories will be proposed defining low-, medium- and high-risk groups based on the predictive risk score considering the highest sensitivity corresponding to an adequate level of specificity. This category definition will help the clinician with the choice to treat individuals with MCI based on the likelihood of converting to dementia in the following 3 years. Because avoiding the clinical consequence of treating a false positive is a target as important as treating a true positive, a rate of false positives less than 20% (i.e. specificity of at least 80%) is considered acceptable for a medium–high-risk group. We will start by inspecting deciles of the predictive score and grouping them into homogeneous classes based on levels of sensitivity and specificity. Kaplan–Meier curves will be presented for each risk group.

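### Accuracy measures, ROC cut-offs, NRI, the calibration plot and the risk-group sensitivity and specificity are written for a known binary outcome, with no rule for people censored before 3 years

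*SAP article*

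**What the plan says.** Under Primary outcome, follow-up ends at conversion, end of follow-up, death or loss, whichever is first. Under Sample size: "Assuming a dropout rate of 20%, a total sample of 500 individuals with MCI has been determined", and "it was verified that 400 evaluated individuals would ensure an acceptable level of precision" for sensitivity and specificity. Statistical analysis method defines the analysis set by baseline biomarker assessment alone, not by completed follow-up.

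The measures in question are these:

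- **Biomarker accuracy (Predictive performance):** "the accuracy measures (sensitivity, specificity, positive predictive value, negative predictive value, overall accuracy, positive and negative likelihood ratios) will be calculated", with an AUC for continuous biomarkers.
- **Cut-offs (Statistical analysis method, after Table 3):** ROC curves "will be used to identify new optimal cut-offs for the specific population under study".
- **NRI (Predictive performance):** defined through net proportions among events and among non-events.
- **Calibration plot (Predictive performance):** made "by plotting the observed outcome proportion" against predicted risk by quantile.
- **Risk score (Model presentation and risk groups):** "Sensitivity and specificity corresponding to different thresholds of the prediction risk score will also be provided for the final model". Deciles are then grouped on these values, with a specificity of at least 80% regarded as acceptable for a medium-high-risk group.

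None of these entries names a method for people censored before 3 years. Missing data deals with predictors; the outcome appears there only as a covariate of the imputation model. Elsewhere the plan does account for censoring: the Cox models, Harrell's c-index, Kaplan-Meier curves by risk group, and a Fine and Gray sensitivity analysis for death. The Brier score is fixed at 3 years, but no censoring weights are named.

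**The concern.** A 2×2 table needs a converter or non-converter status for each person. Someone lost at month 12 without conversion has neither at 3 years. The analyst must count that person as a non-converter or leave the person out, and the plan does not say which.

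The first choice puts unseen converters among the non-converters. The second removes people who would have stayed free of AD more often than people who would have converted, because an early converter is counted before any later loss can occur. Either way, observed risk, PPV and NPV shift even when dropout is unrelated to prognosis. Specificity shifts under the first choice, and under the second if dropout is related to the marker.

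Two analysts following the text could therefore report different accuracy tables, different ROC cut-offs and a different decile boundary for the group meant to inform treatment choice.

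**Working it through.** **1. The plan's own figures.** 400/(1 − 0.20) = 500, as stated. Half-width for a specificity of 80%: 1.96·√(0.8·0.2/(400·(1 − incidence))). At 40% incidence this is 1.96·√(0.16/240) = 5.1 points; at 27% it is 1.96·√(0.16/292) = 4.6 points. Both agree with Table 2, and the other cells reproduce too. No sample-size figure is wrong.

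**2. Inputs.** From Sample size: 3-year incidence 40%, sensitivity 80%, dropout 20%. Assumed here: specificity 80%; exponential conversion times; dropout times uniform over 3 years; conversion time among converters unrelated to the marker.

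**3. Who is censored.** Cumulative hazard a = −ln(0.6) = 0.5108. Probability of being unconverted at a uniform dropout time: 0.40/0.5108 = 0.7831.

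- Unknown status: 0.20 × 0.7831 = 15.7% of participants.
- Converters lost before conversion: 0.20 × (0.7831 − 0.60) = 0.0366.
- Non-converters lost: 0.20 × 0.60 = 0.12.
- Conversions observed: 0.40 − 0.0366 = 0.3634.

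**4. Independent dropout of 20%.** Truth: PPV = 0.32/(0.32 + 0.12) = 72.7%; NPV = 0.48/(0.48 + 0.08) = 85.7%.

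| | Truth | Censored = non-converter | Censored excluded |
|---|---|---|---|
| Observed risk | 40% | 36.3% | 0.3634/0.8434 = 43.1% |
| PPV | 72.7% | 0.2907/0.44 = 66.1% | 0.2907/(0.2907 + 0.096) = 75.2% |
| NPV | 85.7% | 0.4873/0.56 = 87.0% | 0.384/(0.384 + 0.0727) = 84.1% |
| Specificity | 80% | 0.4873/0.6366 = 76.5% | 0.384/0.48 = 80.0% |
| Sensitivity | 80% | 80.0% | 80.0% |

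Here 0.2907 = 0.8 × 0.3634; 0.4873 = 0.48 + 0.2 × 0.0366; 0.096 = 0.8 × 0.12; 0.384 = 0.8 × 0.48; 0.0727 = 0.2 × 0.3634.

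**5. Half that dropout.** With 10% dropout, 7.8% have unknown status. PPV reads 69.4% (−3.3 points) or 73.9% (+1.1); specificity reads 78.2% or 80.0%.

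**6. Dropout related to the marker (assumed 30% if positive, 10% if negative).** Of the converters who would drop out, a share (0.7831 − 0.60)/0.40 = 0.4576 is lost before conversion.

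- Observed conversions: 0.32 × (1 − 0.3 × 0.4576) = 0.2761 in positives and 0.08 × (1 − 0.1 × 0.4576) = 0.0763 in negatives; sensitivity 0.2761/0.3524 = 78.3%.
- Specificity, censored as non-converters: (0.48 + 0.08 × 0.0458)/0.6476 = 74.7%.
- Specificity, censored excluded: 0.432/(0.432 + 0.084) = 83.7%.

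**7. A second model.** A simulation used a continuous score (c-index about 0.78 to 0.80), 6-monthly visits and a threshold at a true specificity of 80%.

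- Independent 20% dropout, 40% incidence: true PPV 70.7% read 64.3% (non-converters) or 73.3% (excluded). Specificity read 77.1% or 80.0%. Sensitivity read 73.2% against a true 72.6% under both.
- Independent 20% dropout, 27% incidence: true risk in the top decile was 0.845 and read 0.773 or 0.862.
- Dropout rising with the score (log hazard ratio 0.5 per SD, assumed): specificity read 75.5% to 77.0% or 82.0% to 82.3%.
- Inverse-probability-of-censoring weighting (IPCW) recovered all four true values under independent dropout.

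**The case against.** The strongest reply is that a condensed article's silence does not specify a naive analysis. The observed proportion in a calibration plot could be a Kaplan-Meier estimate, and the NRI sentence is a generic definition. The 400 evaluated out of 500 suggests, without saying so, that dropouts leave the 2×2 table, which is the handling kindest to specificity. The 20% may partly cover missing biomarker assessments, and telephone contact and remote visits are planned to limit loss.

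Much of this stands, and it rules out four stronger readings that a reader might infer.

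- *The plan ignores censoring outside the c-index.* It does not: the Cox models, Kaplan-Meier curves and Fine and Gray analysis handle it.
- *The 80% specificity figure is biased as planned.* It need not be: excluding dropouts leaves specificity at 80.0% under independent dropout.
- *Bias could carry a single biomarker across the 80% line.* That guide concerns the final risk score. The biomarker accuracy table is for comparison with the literature, and biomarkers are selected by Cox stepwise regression.
- *The new ROC cut-offs enter the model.* They may, but Statistical model and variable selection compares forms first and prefers the Table 3 thresholds when little performance is lost.

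The reply does not remove the gap. The article presents itself as a detailed analysis plan and names survival methods in several places, but gives none for these measures. Neither simple handling gives correct PPV, NPV or observed risk in the independent-dropout calculations.

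**Conclusion.** The point holds as a should-fix. For PPV, NPV and observed risk, either simple handling is off by a few points: at 20% independent dropout and 40% incidence, PPV moves by −6.7 or +2.5 points and observed risk by −3.7 or +3.1. At 10% dropout the PPV shifts are −3.3 and +1.1.

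For specificity the conclusion is a risk of bias. There is none if dropouts are excluded and dropout is unrelated to the marker; sensitivity is then unbiased too, or within about 0.6 points when higher scores also mean earlier conversion. Otherwise a true specificity of 80% can read about 75% to 84%, the extremes resting on the assumed 30% versus 10% dropout. That is about the planned half-width of 4.6 to 5.1 points, enough to place a decile boundary on the wrong side of 80%.

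The sizes rest on exponential conversion, uniform dropout and all of the 20% occurring during follow-up. None of these is stated in the plan.

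**What to change.** State in the SAP that the affected measures refer to 36 months and use censoring-aware estimators:

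- **Biomarker accuracy, ROC curves, cut-offs and risk-score thresholds:** time-dependent sensitivity, specificity, PPV, NPV and AUC by IPCW or a Kaplan-Meier-based method. Where dropout may depend on baseline characteristics, estimate the weights from those covariates.
- **Calibration plot:** observed risk within each quantile by Kaplan-Meier, or by Aalen-Johansen if death is treated as competing.
- **Brier score:** IPCW version at 36 months.
- **NRI:** a survival-based estimator, or omit it.
- **Deaths before 36 months:** say whether they are censored or counted as non-conversions, and apply this consistently.

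The number lost before 36 months, by risk-score group, should be reported beside these results.

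The cost is SAP wording and a little more analysis work; intervals will be slightly wider. No new data are needed, and the 80% guide itself is untouched.
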